## Abstract

**Background:**

Patellar mobilization technique during total knee replacement (TKR) has been debated, with some suggesting that lateral retraction, rather than eversion, of the patella may be beneficial. This randomized controlled trial was to investigate the effects of patellar eversion on functional outcomes in TKR.

**Methods and analysis:**

This single-center, prospective, randomized controlled test will be conducted in Jingjiang People's Hospital. Primary end-stage osteoarthritis patients that prepared for unilateral TKR were randomized to one of two patellar exposure techniques during the primary total knee arthroplasty: lateral retraction or eversion. The informed consent will be acquired in each patient. The primary outcome was operation time, length of hospital stay, and straight leg raising time. Second outcomes including Insall-Salvati ratio; range of motion at 1 month, 3 months, and 1 year following TKR; visual analog scale (VAS) at 1 month, 3 months; and Knee Society Score (KSS) score at 1 year following TKR. The significance level was defaulted as P < .05.

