### Study design

This single-center, prospective, randomized controlled test will be conducted in Jingjiang People's Hospital. The sample size was based on the ability to detect a clinically important difference in postoperative quadriceps strength between groups. The protocol was approved by ethics committee of Jingjiang People's Hospital (JJHS-2019-527). Written informed consent will be obtained from each participating patient.

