### Randomization and blind

Once the patients have read and signed the informed consent, those who have met the inclusion criteria will be randomly assigned to one of the two intervention groups: patellar eversion group (n = 50) and patellar retraction group (n = 50).

A computer-generated, permuted-block randomization scheme with a 1:1 ratio between the intervention and control groups will be used, and the software program Stata 14 (Stata Corp LLC, College Station, TX, USA) will be used to carry out the randomization. The allocation will be concealed using sealed and opaque envelopes, numbered consecutively. An independent researcher who will not participate in other study procedures will perform the randomization process. The flow diagram of the study is summarized in Fig. 1.

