### Outcome assessment

Short-term outcomes were as follows: operation time, length of hospital stay, and straight leg raising time. Long-term clinical effect mainly including Insall-Salvati ratio; range of motion at 1 month, 3 months, and 1 year following TKR; and visual analog scale (VAS) at 1 month, 3 months, and Knee Society Score (KSS) score [12, 13] at 1 year following TKR. The ISR Insall-Salvati ratio is the ratio between the length of the patellar tendon and length of the patella. Visual analog scale (0-100 mm): The patients were asked to mark a standardised 100 mm visual analog scale (VAS) ranging from 0 to 100.

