### Data analysis

All statistics were done using SPSS 21.0 (IBM SPSS Statistics for Windows, Version 21.0, Chicago, IL, USA) software. Results for normally distributed continuous variables are expressed as the mean value ± standard deviation, and continuous variables with nonnormal distribution are presented as median values and interquartile range. The statistical analysis was done using a two-tailed Student’s t test. P < 0.05 is considered statistically significant.

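### Three primary outcomes share one undivided two-sided 0.05 level, and the article does not say whether one or all of them must be significant

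*Protocol article*

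**What the plan says.** The abstract, under Methods and analysis, defines the primary endpoint in the singular but lists three variables: "The primary outcome was operation time, length of hospital stay, and straight leg raising time". It then gives one threshold: "The significance level was defaulted as P < .05". A separate group of secondary outcomes follows the primary ones.

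In the body, Outcome assessment lists the same three variables without the word primary: "Short-term outcomes were as follows: operation time, length of hospital stay, and straight leg raising time". The abstract's secondary outcomes appear there as the long-term group.

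Data analysis names the test and repeats the threshold: "The statistical analysis was done using a two-tailed Student’s t test" and "P < 0.05 is considered statistically significant".

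Study design gives the basis of the sample size: "The sample size was based on the ability to detect a clinically important difference in postoperative quadriceps strength between groups". Quadriceps strength is not one of the three primaries, nor is it among the other listed outcomes. Randomization and blind fixes 50 patients per arm.

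The article gives no order of testing, no lead primary, no division of the 5% level, and no statement of how many primaries must be significant.

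**The concern.** The three primaries measure different things: a surgical process time, a discharge measure and an early functional milestone. Each is compared between arms by a two-sided t test against 0.05. Read literally, the text lets any one of the three results support a claim on the primary outcome. That gives three chances of a false positive rather than one.

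The outcomes could also disagree. One technique might shorten surgery while the other brings an earlier straight leg raise. This is only a possibility, but the article has no rule for what would then be concluded, although its stated aim is to guide clinical practice. A rule left open can be chosen once the results are known, and the 5% level then no longer describes the risk attached to the trial's main conclusion.

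**Working it through.** **Inputs from the article**
- Number of primaries: 3 (abstract).
- Level: 0.05, two-sided, stated once for all tests (abstract; Data analysis).
- Arm size: 50 and 50 (Randomization and blind).

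**Assumed, because the article does not give it**
- A common correlation between the three test statistics, varied from 0 to 1.

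**The article's own figure.** One test at 0.05 has a false positive rate of 5.0%. The article states this level and no familywise figure, so there is nothing further to reproduce.

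**Rule A: any one significant primary counts as success**
- Independent tests: 1 - (1 - 0.05)^3 = 1 - 0.857375 = 0.1426, or 14.3%.
- Bound under any dependence (Bonferroni): 3 × 0.05 = 15%.
- For two-sided tests on jointly normal statistics, the Sidak inequality makes 14.3% the ceiling.

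**Rule B: all three must be significant.** The probability that all three are significant cannot exceed the probability for any single one. If at least one of the three has no true difference, the false positive rate of the joint claim is therefore at most 5%.

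Simulation with no true difference on any outcome (2,000,000 draws of three equicorrelated normal statistics, each tested two-sided at 0.05):

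| Assumed correlation | Rule A: at least one significant | Rule B: all three significant |
|---|---|---|
| 0 | 14.2% | 0.01% |
| 0.3 | 13.6% | 0.09% |
| 0.5 | 12.5% | 0.3% |
| 0.7 | 11.0% | 0.9% |
| 0.9 | 8.4% | 2.3% |
| 1.0 | 5.0% | 5.0% |

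The 14.2% at correlation 0 agrees with the exact 14.3% within simulation error. Negative correlation does not raise the figure: at -0.2 Rule A gives 13.9%.

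**Effect of the remedy on error.** The strictest Holm step is 0.05/3 = 0.0167. Three independent tests at that level give 1 - (1 - 0.0167)^3 = 4.9%, and Holm keeps the familywise rate at or below 5% under any dependence.

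**Effect of the remedy on power.** The detectable standardised difference at 80% power with 50 per arm is approximately (z for alpha/2 + z for power) × sqrt(2/50):
- alpha 0.05: (1.960 + 0.842) × 0.2 = 0.56 SD.
- alpha 0.0167: (2.394 + 0.842) × 0.2 = 0.65 SD.

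With the t distribution on 98 degrees of freedom these become 0.57 and 0.66 SD. Put another way, for a true difference of 0.56 SD, power at the strictest Holm step is 66% instead of 80% (normal approximation).

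**The case against.** **An adjustment may sit in a document not shown.** A journal article condenses the full protocol, and methods of multiplicity control are often left to the analysis plan. Silence on such a method would not by itself be a finding. But here the article does not leave the matter untouched. It fixes three primaries, states one undivided level twice, and gives a sample size basis that points to none of them. What stands of the objection is that the article nowhere says p-values will go uncorrected, so the point must be confined to what is fixed and left open in the text.

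**The inflation depends on an assumed rule.** This is correct. The 14.3% applies only if one significant primary is enough. An all-three rule would bring no inflation. The article states neither.

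**A reader might infer that the plan breaks an error rate that it claims.** The text does not support this. Its 5% is a per-test significance level, which a valid t test holds; no familywise rate is promised anywhere.

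**A reader might infer that all listed comparisons have equal standing,** because Outcome assessment drops the word primary, and might compute an error rate over all ten of them (1 - 0.95^10 = 40% if independent). This does not hold. The abstract ranks the outcomes, and Outcome assessment keeps the same two groups under the labels short-term and long-term. The change of label is worth correcting, but it does not turn the secondary outcomes into further routes to a primary claim.

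**The cost cannot be checked against the planned power.** This is true as far as it goes: no difference, SD or power is given. The cost can still be expressed in SD units from the arm size alone, and it compares the remedy with the present testing level.

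**Conclusion.** The point holds in this form: three primary outcomes share one two-sided 0.05 level, and the article does not say how they combine into a conclusion. If any one suffices, the chance of at least one false positive primary is 14.3% under independence and about 11% at a correlation of 0.7. If all three are required, it is at most 5%. The range rests on assumed correlations and on jointly normal test statistics; the article gives no information on how the three outcomes are related. The conclusion does not extend to the secondary outcomes, and it does not say that the plan misstates its own error rate.

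**What to change.** Amend the abstract, Outcome assessment and Data analysis so that they agree on one of two options:

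1. Name one of the three as the primary outcome, tested at two-sided 0.05, and make the other two secondary.
2. Keep all three as primary and apply Holm: compare the smallest p-value with 0.0167, the next with 0.025 and the largest with 0.05, stopping at the first that fails.

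In either case, use the abstract's primary and secondary labels in Outcome assessment as well, so that the short-term and long-term headings do not stand in for the ranking.

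The cost is wording plus, under option 2, some power. At 50 per arm the difference detectable at 80% power for a primary rises from about 0.57 SD to at most about 0.66 SD. The higher figure is the worst case, because later Holm steps are less strict. Option 1 costs no power on the chosen outcome, since it is still tested at 0.05. Whether 50 per arm is enough for that outcome cannot be judged from the article, because its sample size rests on quadriceps strength and no difference, SD or power is given.

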**Results:**

Results will be published in relevant peer-reviewed journals.

**Conclusion:**

Our study aims to systematically assess the functional outcomes of patellar eversion for TKR patients, which will provide clinical guidance for TKR patients.

## Introduction

Total knee replacement (TKR) is among the most common elective procedures performed worldwide [1, 2]. However, up to 20% of patients are dissatisfied or not completely satisfied with the outcome of TKR [3]. In order to make patients more satisfied with the TKR, minimally invasive TKR was introduced and widely applied in the TKR surgeries [4]. It was reported that minimally invasive TKR obtained less blood loss, less loosening of lateral soft tissues, shorter hospital stay, and faster recovery of quadriceps [5].

The patella everted can augment surgical exposure and has been a routine part of surgical technique [6]. Lateral retraction of the patella is an alternative technique for TKR [7]. There is ongoing debate regarding whether or not the patella should be everted during TKR [8]. Zan et al. [9] conducted a meta-analysis and found that no difference in clinical outcome between patella eversion and lateral retraction in TKR. Jenkins et al. [10] found that lateral retraction of the patella did not lead to superior postoperative results compared with eversion of the patella during TKR. Reid et al. [11] found that retracting rather than everting the patella during TKR resulted in no significant clinical benefit in the early to medium-term follow-up. In current literature, there are limited randomized studies that specifically evaluate the results of patellar eversion versus patellar retraction during the TKR.

We thus designed a prospective, randomized controlled trial of 2 groups of patients treated with patellar eversion versus patellar retraction for TKR patients. Our goal was to compare functional outcomes at short-term and long-term follow-up between the two groups and finally provide clinical guidance for TKR patients.

## Methods and analysis

This study was registered in Research Registry (No: researchregistry6814).

### Participants

Patients with these conditions will be included (1) end-stage osteoarthritis patients; (2) primary unilateral TKR patients; (3) varus deformity or valgus deformity < 20°; and (4) the follow-up time was set to be at least 1 year after the surgical procedure. Exclusion criteria include (1) revision TKR; (2) previous knee surgery; (3) body mass index (BMI) ≥ 40.0 kg/m^2^; and (4) history of cardiovascular disease inability to tolerate the TKR procedure.

### Study design

This single-center, prospective, randomized controlled test will be conducted in Jingjiang People's Hospital. The sample size was based on the ability to detect a clinically important difference in postoperative quadriceps strength between groups. The protocol was approved by ethics committee of Jingjiang People's Hospital (JJHS-2019-527). Written informed consent will be obtained from each participating patient.

### Randomization and blind

Once the patients have read and signed the informed consent, those who have met the inclusion criteria will be randomly assigned to one of the two intervention groups: patellar eversion group (n = 50) and patellar retraction group (n = 50).

A computer-generated, permuted-block randomization scheme with a 1:1 ratio between the intervention and control groups will be used, and the software program Stata 14 (Stata Corp LLC, College Station, TX, USA) will be used to carry out the randomization. The allocation will be concealed using sealed and opaque envelopes, numbered consecutively. An independent researcher who will not participate in other study procedures will perform the randomization process. The flow diagram of the study is summarized in Fig. 1.

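### The primary outcomes are committed to an unadjusted t test although BMI and deformity must be assessed before randomisation; if these factors are prognostic, a pre-specified linear model would be more precise at almost no cost

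*Protocol article*

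**What the plan says.** The abstract of the protocol article names the primary outcomes: "The primary outcome was operation time, length of hospital stay, and straight leg raising time". The section Outcome assessment lists the same three as short-term outcomes.

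The section Data analysis names a single test, with no covariate or model: "The statistical analysis was done using a two-tailed Student’s t test". The threshold is "P < 0.05 is considered statistically significant".

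The section Participants makes two patient characteristics part of eligibility. One inclusion criterion is "varus deformity or valgus deformity < 20" (degrees), and one exclusion criterion is "body mass index (BMI) ≥ 40.0 kg/m" (squared). Both must therefore be assessed before a patient is randomised.

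The section Randomization and blind describes the allocation: "A computer-generated, permuted-block randomization scheme with a 1:1 ratio between the intervention and control groups will be used". It plans 50 patients per group. It names no stratification factor, and it does not say that there is none.

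**The concern.** None of the three primary outcomes has a preoperative value of its own, so the usual gain from adjusting a score for its baseline is not available. Other patient characteristics known before surgery are what remains for reducing residual variance, and the eligibility criteria already call for two of them. It is plausible that BMI and deformity affect how hard a knee is to expose, and hence operation time. That is a clinical inference, not a statement in the article.

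If the inference is right, a plain t test leaves explainable variation in the error term, and the interval around the primary effect is wider than the same 100 patients could give. The article does not show that precision for the primary outcomes is adequate. The stated basis for the sample size is a different variable: "The sample size was based on the ability to detect a clinically important difference in postoperative quadriceps strength between groups". Quadriceps strength is not among the listed outcomes.

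**Working it through.** **Inputs from the protocol article.** 50 per arm (100 in total), 1:1; two-sided test at 0.05; no covariates.

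**Inputs not in the article.** It gives no difference, SD, power or dropout, so the figure of 50 per arm can be neither reproduced nor refuted. R², the share of outcome variance explained by BMI and deformity together, is not given either. It is assumed here over 0 to 0.30.

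**Step 1: what the t test can detect.** The detectable standardised difference is (z for alpha + z for power) × √(2/50).
- 80% power: (1.960 + 0.842) × 0.2 = 0.560 SD.
- 90% power: (1.960 + 1.282) × 0.2 = 0.648 SD.

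The value 0.56 SD serves below only as a reference point at which the planned test has 80% power. It is not a design target of the trial.

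**Step 2: the effect of adjustment.** With p = 2 covariates and n = 100, the variance of the treatment effect is multiplied by (1 − R²) × [1 + p/(n − p − 3)] = (1 − R²) × (1 + 2/95) = (1 − R²) × 1.021. The SE ratio is the square root of this. Power is Φ(2.802/SE ratio − 1.960), and the equivalent number of unadjusted patients is 100/variance ratio.

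| Assumed R² | SE ratio | Power at 0.56 SD | Equivalent total patients | Detectable difference, 80% power |
|---|---|---|---|---|
| t test | 1.000 | 80% | 100 | 0.560 SD |
| 0 | 1.010 | 79% | 98 | 0.566 SD |
| 0.02 | 1.000 | 80% | 100 | 0.560 SD |
| 0.05 | 0.985 | 81% | 103 | 0.552 SD |
| 0.10 | 0.959 | 83% | 109 | 0.537 SD |
| 0.20 | 0.904 | 87% | 122 | 0.506 SD |
| 0.30 | 0.845 | 91% | 140 | 0.474 SD |

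Break-even is where (1 − R²) × 1.021 = 1, which gives R² = 1 − 1/1.021 ≈ 0.02.

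These powers use the normal approximation. At 0.5 SD it gives 70.5% for the t test, against 69.7% from the noncentral t, so it overstates power by less than one point.

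**Step 3: simulation.** There were 6,000 trials per setting, each with 100 patients, a difference of 0.56 SD and two normal covariates sharing R² equally. Allocation was either without strata or in blocks of 4 within four strata (each covariate high or low). Monte Carlo error is about √(0.8 × 0.2/6000) = 0.005 for power and √(0.05 × 0.95/6000) = 0.003 for type I error.

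| R² | Allocation | t test: power / type I error | Adjusted model: power / type I error |
|---|---|---|---|
| 0.1 | no strata | 79.8% / 0.054 | 82.5% / 0.053 |
| 0.1 | strata | 80.0% / 0.040 | 83.1% / 0.049 |
| 0.2 | no strata | 79.4% / 0.046 | 87.2% / 0.046 |
| 0.2 | strata | 80.9% / 0.037 | 87.4% / 0.048 |
| 0.3 | no strata | 79.0% / 0.051 | 90.3% / 0.049 |
| 0.3 | strata | 81.5% / 0.032 | 91.0% / 0.049 |

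The gain comes from the model. It is nearly the same with and without strata. Stratifying while keeping the t test adds at most 81.5 − 79.0 = 2.5 points and makes the test conservative.

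**The case against.** The strongest reply is that the planned test is valid. Under randomisation it is unbiased, and it kept its type I error in the simulation. Many sound trials use it. The article also never says that BMI or deformity predicts any primary outcome. Both points stand. The case is therefore conditional: with R² below about 0.02 nothing is gained, and at R² = 0 about one power point is lost.

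A second reply is that a condensed article may leave covariates to a fuller document. That would answer a complaint about silence. Here the article does name its method, and the method is unadjusted.

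A reader might infer more than the article supports:
- **That allocation runs from one unstratified list.** The text names no strata but does not rule them out, and an article may leave that detail to the full protocol. The point does not depend on it.
- **That differences between surgeons threaten the result.** The article does not say how many surgeons operate or how much they differ, so no size can be given. With one surgeon the issue does not arise.
- **That chance imbalance in difficult knees is a further, uncorrected harm.** The standard error of the t test already covers it. Residual variance and chance imbalance are one loss described twice.

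Two practical objections also stand. The criteria can be applied as threshold checks, so the article does not show that actual BMI values, degrees or direction of deformity are recorded. The power figures hold for a linear model with roughly normal errors and do not carry over to a skewed hospital stay or to a proportional-odds model.

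**Conclusion.** The point holds as a conditional gain in efficiency, not as an error of validity. The article fixes an unadjusted t test for outcomes that have no baseline of their own, while two plausible covariates must be assessed before randomisation. At 50 per arm and 0.56 SD, a pre-specified linear model costs about 1 power point if the covariates explain nothing. It gains about 3, 7 and 11 points at R² of 0.10, 0.20 and 0.30. This rests on the assumed R², on two covariates, on roughly normal errors and on the reference difference of 0.56 SD, none of which the article gives. The evidence supports a change to the stated analysis. It does not support a criticism of the randomisation.

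**What to change.** In Data analysis, replace the t test for operation time with a linear model on arm, BMI and deformity, and report the adjusted mean difference with its 95% CI. Name the covariates and their form before any outcome is seen. Use the same covariates for hospital stay and straight leg raising time, on a log scale if skewed. Add surgeon to the model only if more than one operates. Allocation need not change; if any factor is or has been used to stratify it, keep that factor in the model.

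The cost is a few degrees of freedom out of 98, and BMI and deformity must be recorded as values rather than only checked against the limits. No extra patients or visits are needed.

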**Fig. 1 Fig1:**
[figure not shown]
The flow diagram of a procedure to select studies

### Outcome assessment

Short-term outcomes were as follows: operation time, length of hospital stay, and straight leg raising time. Long-term clinical effect mainly including Insall-Salvati ratio; range of motion at 1 month, 3 months, and 1 year following TKR; and visual analog scale (VAS) at 1 month, 3 months, and Knee Society Score (KSS) score [12, 13] at 1 year following TKR. The ISR Insall-Salvati ratio is the ratio between the length of the patellar tendon and length of the patella. Visual analog scale (0-100 mm): The patients were asked to mark a standardised 100 mm visual analog scale (VAS) ranging from 0 to 100.

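### The long-term functional conclusion can come only from seven unranked secondary comparisons, each called significant at an unadjusted P < 0.05; the chance of at least one false positive is about 11% to 30%, depending on a correlation that is not given

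*Protocol article*

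**What the plan says.** The abstract of the protocol article names three primary outcomes: operation time, length of hospital stay and straight leg raising time. It then lists "Second outcomes including Insall-Salvati ratio; range of motion at 1 month, 3 months, and 1 year following TKR", together with "visual analog scale (VAS) at 1 month, 3 months; and Knee Society Score (KSS) score at 1 year following TKR". The Outcome assessment section gives the same outcomes but sorts them by time rather than by rank. The three primaries form the short-term group, and the rest are introduced as "Long-term clinical effect mainly including Insall-Salvati ratio; range of motion at 1 month, 3 months, and 1 year following TKR", with VAS and KSS following.

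On testing, the abstract states "The significance level was defaulted as P < .05". The Data analysis section states "The statistical analysis was done using a two-tailed Student’s t test" and "P < 0.05 is considered statistically significant". Neither place separates primary from secondary outcomes, sets an order, or says which visit or scale decides.

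The aim in the Introduction is "Our goal was to compare functional outcomes at short-term and long-term follow-up between the two groups and finally provide clinical guidance for TKR patients". The Discussion repeats that the trial is meant to reach a conclusion on both short-term and long-term function.

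**The concern.** Half of the stated aim is long-term function, yet all three primary outcomes are short-term by the article's own grouping. Any long-term conclusion must therefore be drawn from the secondary list. That list has seven entries of equal standing, and the article declares each of them significant at an unadjusted 5%.

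Two things are at stake. First, with seven chances, a single significant result is much more likely to arise by chance than the 5% threshold suggests to a reader. Second, the entries can disagree. Range of motion might differ at 1 month while KSS at 1 year shows nothing, and the plan does not say which result settles the question. Range of motion alone has three visits with no deciding one. Resolving multiplicity among the three primaries would leave both problems in place.

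**Working it through.** **Inputs from the article**

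- Secondary comparisons (Abstract; Outcome assessment): Insall-Salvati ratio 1, range of motion 3, VAS 2, KSS 1. Total 1 + 3 + 2 + 1 = 7.
- Strictly functional comparisons among them: range of motion 3 and KSS 1, total 4. The Insall-Salvati ratio is defined in Outcome assessment as a ratio of two lengths, and VAS is a separate patient-marked scale.
- Test (Data analysis): two-sided, 0.05 each.
- Correlation between outcomes: not given, so it is varied here as an assumption.

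The article states no familywise error rate, so there is no figure of its own to reproduce. The only stated figure is the per-test 5%.

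**Independent tests, no true difference**

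P(at least one significant) = 1 − 0.95^k.

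- k = 7: 1 − 0.95^7 = 1 − 0.698 = 30.2%. The upper bound under any dependence is 7 × 0.05 = 35%.
- k = 4: 1 − 0.95^4 = 1 − 0.815 = 18.5%. The upper bound is 4 × 0.05 = 20%.

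**Correlated tests**

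Each statistic is z_j = √ρ·s + √(1 − ρ)·e_j, with s and e_j independent standard normal. A test is significant if |z_j| > 1.96. Results from 1,000,000 simulated draws per row (the first row is the exact formula):

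| Assumed common correlation ρ | Seven tests | Four functional tests |
|---|---|---|
| 0 | 30.2% | 18.5% |
| 0.3 | 27.1% | 17.4% |
| 0.5 | 23.0% | 15.6% |
| 0.7 | 17.7% | 13.0% |
| 0.9 | 11.5% | 9.4% |

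**Check with a less uniform pattern**

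One correlation was used between visits of the same scale (0.5 to 0.8) and a lower one between scales (0 to 0.5). Across the combinations tried, the seven-test rate ran from 21.7% to 28.3%.

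**Range of motion alone, three visits**

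1 − 0.95^3 = 14.3% if independent; by simulation, 12.6% at ρ = 0.5 and 10.9% at ρ = 0.7.

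**With one deciding contrast**

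The error rate for the long-term conclusion, taken on its own, is the stated 5%.

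**The case against.** The strongest reply is that ordering and adjusting secondary outcomes is normally left to an analysis plan, which is not shown, and that a condensed article need not repeat it. The abstract does rank these outcomes below the primaries, and a general P < 0.05 line is an ordinary per-test convention. This stands as far as it goes: the missing hierarchy alone would not be a finding. The point survives because the article does more than stay silent. It fixes one significance rule for every outcome and sets a long-term functional aim that no primary outcome can answer. The secondaries are then not merely supportive of a long-term primary result, because there is none.

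Other parts of the reply also stand and limit the point:

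- A reader might infer that the whole functional conclusion rests on the seven. It does not. The aim covers short-term function too, and straight leg raising time is a primary outcome.
- A reader might take 23% as the error rate of the plan. It is the value at an assumed correlation of 0.5, and the article gives no correlation.
- A reader might treat all seven as functional tests. Strictly, only four are, although the article puts all seven in its long-term group.
- A reader might infer a rule that any one significant secondary will be turned into guidance even if all primaries are null. No such rule is written. The text leaves that route open but does not prescribe it.
- Testing a key secondary only after the primary analysis succeeds would not work as the plan stands, since success on three unranked primaries is undefined. It could also block the long-term question because of a null result on operation time or length of stay.

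**Conclusion.** The point holds for the long-term part of the aim. That conclusion can come only from seven unranked secondary comparisons, each called significant at an unadjusted 5%. If there is no true difference on any of them, the chance of at least one significant result is about 30% under independence, 23% at a correlation of 0.5 and 11% at 0.9. Restricted to the four strictly functional tests, it is about 19%, 16% and 9%. All correlations are assumptions, and the rates count a false positive in either direction. Even the lowest figure is nearly twice the nominal 5%.

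The documents do not support a single figure for the error rate, nor a claim that the short-term functional result is affected in the same way. The defect bears on what may be concluded, not on the conduct of the trial. The three unadjusted primary outcomes are a separate matter and are not assessed here.

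**What to change.** In the abstract, Outcome assessment and Data analysis sections, before any comparison between arms is seen:

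1. The sponsor names one long-term functional contrast that is already collected as the deciding one for the long-term conclusion, tested at two-sided 0.05. KSS at 1 year is one example; the choice is the sponsor's.
2. The other six secondary comparisons are labelled supportive or exploratory and reported as mean difference with 95% confidence interval, without a claim of significance.
3. The sentence that sets P < 0.05 as significant is limited to the primary analysis and the deciding contrast.
4. Testing of that contrast is not made conditional on the primary analysis, unless a rule for primary success is defined first.

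The cost is wording only, with no added patients, visits or data. The downside is that an isolated P < 0.05 on another secondary can no longer be claimed as a significant finding. Step 1 holds the long-term conclusion at 5% on its own; it does not control error jointly with the primaries.
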